## Abstract

**Background:**

Communication is one of the most important predictors of social reintegration after stroke. Approximately 15–42% of stroke survivors experience post-stroke aphasia. Helping people recover from aphasia is one of the research priorities after a stroke. Our aim is to develop and validate a new therapy integrating dubbing techniques to improve functional communication.

**Methods:**

The research project is structured as three work packages (WP). WP1: development of the dubbed language cinema-based therapy: Two research assistants (a speech therapist and a dubbing actor) will select the clips, mute specific words/sentences in progressive speech difficulty, and guide patients to dub them across sessions. Words to be dubbed will be those considered to be functionally meaningful by a representative sample of aphasic patients and relatives through an online survey. WP2: a randomized, crossover, interventional pilot study with the inclusion of 54 patients with post-stroke non-fluent aphasia. Patients will be treated individually in 40-min sessions twice per week for 8 weeks. Primary outcomes will be significant pre/post differences in scores in the Communicative Activity Log (CAL) questionnaire and Boston Diagnostic Aphasia Examination (BDAE) administered by a psychologist blinded to the patients’ clinical characteristics. Secondary outcomes: General Health Questionnaire (GHQ)-12, Stroke Aphasia Quality of Life Scale (SAQOL-39), Western Aphasia Battery Revised (WAB-R), and the Stroke Aphasic Depression Questionnaire (SADQ10). WP3: educational activities and dissemination of results. WP3 includes educational activities to improve public knowledge of aphasia and dissemination of the results, with the participation of the Spanish patients’ association *Afasia Activa*.

**Discussion:**

This pilot clinical trial will explore the efficacy of a new therapeutic tool based on dubbing techniques and computer technology to improve functional communication of patients suffering from post-stroke aphasia with the use of standardized test assessment.

**Trial registration:**

ClinicalTrials.govNCT04289493. Registered on 28 February 2020.

## Background

Stroke is a leading cause of disability, and the absolute number of people who develop stroke each year is growing worryingly, as are the number of survivors and the overall burden of stroke [1]. Communication is a vital aspect of daily functioning, being the most important predictor of social reintegration after a stroke [2]. It is estimated that approximately 15–42% of stroke survivors experience post-stroke aphasia, affecting some of the language modalities, including the production and understanding of speech, reading, and writing. Aphasia is associated not only with a greater risk of mortality after stroke, but also with long-term disability, greatly impacting the quality of life [3]. Hence, helping people recover from aphasia has been identified by consensus among survivors, caregivers, and health professionals as one of the top 10 research priorities relating to life after stroke [4]. Current international guidelines recommend speech and language therapy (SLT) for stroke survivors [5, 6]. However, according to a Cochrane meta-analysis, available SLT differ in therapy regimens (intensity, dosage, duration), delivery models (group, one-to-one, volunteer, computed-facilitated), approach, and outcome measurements [7]. Thus, there is no universally accepted SLT for post-stroke aphasia. Moreover, several SLTs use child-like materials, therefore not being generalizable for a daily adult life. This is one of the main challenges of intensive SLT since it produces high rates of early dropouts, up to 30% [7], as patients do not feel that their preferences are being covered.

Computer-based technology such as mobile apps, video games, and virtual reality is increasingly being used with success in post-stroke motor rehabilitation [8]. However, SLT has not embraced the same path [9]. To our knowledge, the first attempt at using audiovisual material for SLT purposes dates from the 60's. Researchers from the University of Chicago Speech and Language Clinic used film strips with various topics for homebound and outpatient aphasic patients. Patients showed higher engagement with therapy and increased their spontaneous self-expression [10]. Recent studies used videos in SLT for instructional or speech-triggering purposes [11, 12]. Results were positive, with an improvement in patients’ knowledge about aphasia and language skills; however, the scripts used were very limited and the patients reported their wish to have a wider and more varied range of words to practice. Besides, the use of word and sentence imitation in a computer-based intensive therapy improved the narrative production of 19 patients in a before and after trial [13]. Although a randomized clinical trial was designed to assess the effect of intensive imitation therapy (NCT00713050) [14], to our knowledge, no results other than non-randomized case series have been reported from that study [13].

We conducted a PubMed search with the terms (((computer-based) AND (therapy)) AND (stroke)) AND (aphasia), retrieving a total of 25 articles (last search conducted on October 30, 2021). Of these, only five presented the results of randomized clinical trials [15–19], and an additional completed clinical trial was found on the ClinicalTrials.gov website [20] (Table 1). Clearly, we need to change our therapeutic approach in post-stroke aphasia and take advantage of existing technology.

**Table 1 Tab1:** Summary of completed computer-based clinical trials on post-stroke aphasia

Reference	Trial ID	Design	Patients	Interventions	Main results
Kesav P et al. *J Neurol Sci* 2017; 380:137–141 [15]	Clinical Trials registry India 2016/08/0120121	Prospective open randomized, controlled trial with blinded endpoint evaluation.	20	• Group A: less intensive (12 therapy sessions of conventional professional-based SLT) • Group B: more intensive (12 therapy sessions of conventional professional-based SLT + 12 h of computer-based SLT)	• Less intensive worked better, but authors still recommend using computer-based
Grechuta K et al. *Stroke* 2019; 50:1270–1274 [16]	NCT02928822	Randomized, controlled, parallel-group trial	17	• Control group (*N*=8): standard treatment • Experimental group (*N*=9): augmented embodied therapy with the Rehabilitation Gaming System for aphasia.	• Both groups significantly improved on the BDAE and on the lexical access-vocabulary test. • Only the Rehabilitation Gaming System for aphasia group improved on the CAL and showed therapy-induced improvements in language and communication at 16 weeks of follow-up.
Palmer R et al. *Lancet Neurol*. 2019; 18: 821–33 [17]	ISRCTN68798818	Pragmatic, superiority, three-arm, individually randomized, single-blind, parallel-group trial.	278	• Control group: 6 months of usual care (usual care group) • CSLT Group: Daily self-managed CSLT plus usual care • Attention control plus usual care: paper-based puzzle book activities (e.g., sudoku, spot the difference, word searches, or coloring) on a daily basis.	• CSLT plus usual care resulted in a clinically significant improvement in personally relevant word finding but did not result in an improvement in conversation.
Cherney LR et al. *Clin Rehabil* 2021; 35: 976–987 [18]	NCT04413136	Single-blind, randomized placebo-controlled trial	32	• Experimental treatment (*N*=19): Web ORLA (Oral Reading for Language in Aphasia) • Control group (*N*=13): a commercially available computer game. Both groups were instructed to practice 90 min/day, 6 days/week for 6 weeks.	• No significant difference in the gain from pre-treatment to post-treatment between groups. • The Web ORLA group showed significantly greater gains at the 6-week follow-up than the control group.
Spaccavento S et al. *J Communication Disorders* 2021:106158 [19]	NA	Pilot randomized non-inferiority study	22	• Experimental group: computer-based • Control group: therapist-mediated aphasia treatment Both groups received one 50-min session for 5 days per week over a period of 8 weeks.	• Participants in both groups improved in language skills, functional communication, and quality-of-life measures from pre- to post-treatment • No significant differences between groups.
Elhakeem ES et al. *The Egyptian J Otolaryngology* 2021; 37:77 [20]	NCT04717180	Randomized controlled trial with blinded endpoint evaluation	50	• Group I: 48 sessions using the Arabic software program • Group II: 48 sessions of conventional Therapy	• Significant improvement from the baseline in both groups. • No significant difference in post-therapy results between groups except for some secondary items, whereas group I showed more significant improvement (phrase length, melodic line, word-finding relative to fluency, paraphasia, repetition, responsive naming, Boston naming test)

*BDAE* Boston Diagnostic Aphasia Examination, *CAL* Communicative Activity Log, *CSLT* Computer-based Speech and Language Therapy, *NA* not available, *SLT* Speech and Language Therapy

Sources: https://clinicaltrials.gov [search terms (Post-stroke aphasia) AND (computer); filters: completed] and PubMED [(computer-based) AND (therapy) AND (stroke) AND (aphasia)]. Last search conducted on October 30, 2021

## Methods

Our aim is to develop and validate a new therapy integrating dubbing techniques to improve functional communication. This research project is structured as three work packages (WP). WP1: development of the dubbed language cinema-based therapy; WP2: a randomized, crossover, interventional pilot study; WP3: educational activities to improve public knowledge of aphasia and dissemination of the results. Here we present the protocol corresponding to the WP2 (clinical trial).

### Design

A randomized, crossover, interventional pilot study, following the CONSORT guidelines on randomized pilot and feasibility studies [26] and the SPIRIT 2013 Recommendations for Interventional Trials [27].

### Patient population

The Departments of Neurology and Rehabilitation (Speech Therapy Unit) at La Paz University Hospital and “Afasia Activa”, a non-profit patients’ association, will help with recruitment.
Inclusion criteria:
Non-fluent aphasia due to ischaemic stroke in the left hemisphere without neuroimaging evidence of lesions in the right hemisphere;Standard program of conventional speech therapy previously completed;Severely restricted language; poor repetition even for single words and moderately preserved language comprehension (i.e., not exceeding the 70th percentile in Repetition Scale plus exceeding the 15th percentile in Listening Comprehension Scale as an average score in word comprehension and command subscales and complex ideational material) in the Boston Diagnostic Aphasia Examination (BDAE);Signed informed consent. All the patients, or their guardian or legal representative, will be asked to sign a written informed consent form after a detailed explanation of the nature and purpose of this study and before undergoing any of the procedures related to the clinical trial. An aphasia-friendly information sheet containing large text and simplified language will be provided.Exclusion criteria:
Any clinical condition or other characteristics that precluded appropriate follow-up;Simultaneous participation in any therapeutic trial assessing post-stroke recovery.

### Randomization

Upon signature of informed consent, the included patients will be randomly allocated (1:1) to one of the following groups (Fig. 1):
Group 1 (*N*=27): therapy starts within the first 3 months of their inclusion in the study, followed by a subsequent period of 3 months without therapy (washout period), thus serving as controls for the second phase of the study.Group 2 (*N*=27): therapy starts between 3 and 6 months after their inclusion in the study. They do not receive speech therapy treatment during the first 3 months, thus serving as controls for the first phase of the study (waitlist controls) and as the active intervention group in the second phase.

**Fig. 1 Fig1:**
[figure not shown]
Study design

A computer-generated random list of numbers provided by an independent statistician will be used for study allocation. The randomization sequence will be created using SAS V.9.4 statistical software (procedure “PROC PLAN”) with a 1:1 allocation. No randomization seed will be specified. The randomization seed will be generated taking the hour of the computer when the program is executed. Randomization will be performed centrally through an Interactive Web Response System in order to conceal the sequence until interventions are assigned (REDCap 8.7.4 - 2021 Vanderbilt University).

### Intervention

Baseline session: first, evaluation of the baseline patient’s communication skills through BDAE and CAL. Second, to individualize the therapy, the patients and their relatives will select 48 words according to their needs from a list that was constructed by members of stroke and aphasia patients’ associations through an online survey available at https://goo.gl/forms/sxsDH9sicKaFlvas2. Each word has a corresponding 5- to 15-s clip that will be presented during the therapy following the principle of incremental learning (less complex first) using ad hoc designed software very similar to free audio editing software. Finally, the patient will receive training in the basic points of dubbing.Sixteen 40-minute individualized dubbing sessions: one clip is played several times with sound. The dubbing actor explains the context and the speech therapist teaches the patient how to imitate the oral movements of the actor. Then, the target word is muted and the patient is encouraged to dub the gap, regardless of the synchrony, although some indicators may signal when the word should be pronounced. After each recording, the patient is rewarded by watching the dubbed fragment as many times as he/she wants to. We will score the following components: repetition, motor coordination, intonation, and synchrony. They will be evaluated at the end of the therapy considering the following ad hoc criteria for each targeted word: repetition (not achieved, achieved with difficulty, achieved); motor coordination (no impairment, mild impairment, moderate impairment, severe impairment); intonation (appropriate, not appropriate); and synchrony (appropriate, not appropriate).

### Primary outcomes

A psychologist blinded to the patients’ clinical characteristics and his/her allocated group will administer the CAL [28] questionnaire and the BDAE [29] three times per patient. In brief, group 1 will be evaluated after the study group allocation, after the completion of the therapy, and after a washout period of 3 months, whereas group 2 will be evaluated after the study group allocation, after the waitlist period/prior the start of the therapy and after its completion.

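### Baseline CAL and BDAE are taken after allocation although participants cannot be masked; this can bias the phase-1 and pre/post comparisons, but not the phase-averaged crossover effect

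*Protocol article*

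**What the plan says.** The order of events is spread over four sections of the protocol article.

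- **Randomization:** "Upon signature of informed consent, the included patients will be randomly allocated (1:1) to one of the following groups". Group 1 starts therapy within 3 months of inclusion. Group 2 waits, without speech therapy, and starts between 3 and 6 months.
- **Primary outcomes:** "group 1 will be evaluated after the study group allocation, after the completion of the therapy, and after a washout period of 3 months", while "group 2 will be evaluated after the study group allocation, after the waitlist period/prior the start of the therapy and after its completion". Each patient has three assessments, and the first follows allocation in both groups. The same section states the assessor's blinding: "A psychologist blinded to the patients’ clinical characteristics and his/her allocated group will administer the CAL", together with the BDAE.
- **Intervention:** "Baseline session: first, evaluation of the baseline patient’s communication skills through BDAE and CAL". Word selection and training in dubbing follow in the same session.
- **Patient population:** inclusion needs BDAE scores ("not exceeding the 70th percentile in Repetition Scale plus exceeding the 15th percentile in Listening Comprehension Scale"), so part of the BDAE must exist before a patient can be randomised. The article does not call those scores the baseline.

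The first assessment matters to the results. The abstract defines the primary outcomes as pre/post differences in CAL and BDAE, and Statistical analyses describes mixed models that allow adjustment for baseline values.

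**The concern.** A baseline is safe to subtract or adjust for because allocation cannot have influenced it. Here it can. One group starts a new therapy and the other gets no speech therapy for 3 months, and nothing can hide that difference once the allocation is released. Hope or disappointment may colour answers to a questionnaire such as the CAL, or the effort put into a test. A patient who withdraws on learning of the wait leaves no study baseline. The protocol itself expects some reluctance: Sample size estimates says the crossover is meant to reduce refusal of the control group.

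The timing may also differ between groups. The Intervention section puts CAL and BDAE at the head of the session that opens the therapy, and group 1's therapy start can fall anywhere in a 3-month window. The interval from allocation to first assessment is not stated for either group.

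At stake are the comparisons that use the first assessment as a reference point. The distortion could go either way: it could mimic a benefit or hide one.

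**Working it through.** **The plan's own figure.** Sample size estimates gives 27 per arm, 80% power and two-sided 0.050, but no CAL difference or SD, so 27 cannot be reproduced, only inverted. For two parallel means, d = (1.960 + 0.842) × √(2/27) = 0.762 SD (0.777 with the t distribution). Inverted as a paired comparison, it gives 0.560 (n = 27) or 0.388 (n = 54) SDs of the paired difference. The plan does not say which applies.

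**Notation.** A1, A2 and A3 are the three assessments. Let s be the allocation-induced shift in A1, group 1 minus group 2, and r the correlation of A1 with later scores. Assume equal SDs, no true effect, and no effect of the shift on A2 or A3.

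**Where the shift enters.**

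1. *Group 1's pre/post change*, A2 − A1: moved by the full shift in group 1's own baseline. *Group 2's pre/post change*, A3 − A2: not affected, because its pre-therapy value is the second assessment.
2. *Phase-1 comparison, change score*, (A2 − A1) in group 1 minus (A2 − A1) in group 2: bias −s.
3. *Phase-1 comparison, baseline-adjusted*: bias −r × s.
4. *Phase-2 comparison, baseline-adjusted* (group 2 is now the treated group): bias +r × s.
5. *Treatment-by-phase term*, as the difference between the two phase effects: bias −2 × r × s.
6. *Phase-averaged treatment effect*: the mean of items 3 and 4, (−r × s + r × s)/2 = 0. Written out, it is ½{[A2 − A3] in group 1 − [A2 − A3] in group 2}. A baseline adjustment subtracts the same multiple of A1 from A2 and A3 and drops out.

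Item 6 needs complete data and takes the scores themselves as the response, which is how Statistical analyses reads. If the response were the change within each phase, the shift would enter phase 1 only and half of it would remain. If the treatment coefficient were coded as the effect in one reference phase, it would be item 3 or 4, not item 6.

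**Numbers.** Both the shift and r are assumptions, because the document gives neither. Type I error is for the phase-1 comparison with 27 per arm, by normal approximation, with standard error √(2(1 − r) × 2/27) for the change score and √((1 − r²) × 2/27) for the adjusted comparison.

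| r | Shift (SD) | Change-score bias | Type I error | Adjusted bias | Type I error |
|---|---|---|---|---|---|
| 0.5 | 0.1 | 0.10 | 0.066 | 0.05 | 0.055 |
| 0.5 | 0.3 | 0.30 | 0.197 | 0.15 | 0.098 |
| 0.7 | 0.1 | 0.10 | 0.076 | 0.07 | 0.065 |
| 0.7 | 0.2 | 0.20 | 0.158 | 0.14 | 0.111 |
| 0.7 | 0.3 | 0.30 | 0.296 | 0.21 | 0.191 |
| 0.9 | 0.1 | 0.10 | 0.130 | 0.09 | 0.118 |
| 0.9 | 0.3 | 0.30 | 0.693 | 0.27 | 0.624 |

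At r = 0.7 the treatment-by-phase term would move by 2 × 0.07 = 0.14 to 2 × 0.21 = 0.42 SD.

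**Loss before baseline.** Suppose 2, 4, 6 or 8 of the 27 waitlist patients left before baseline and dropped out of the analysis. Power for a parallel comparison at 0.762 SD would fall from 0.80 to 0.784, 0.766, 0.746 or 0.721. The more serious effect would be selection, which these figures do not capture.

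**The case against.** The strongest objection concerns the analysis. A reader might infer that a shifted baseline turns directly into a false treatment effect for the trial. The document does not support that: the model in Statistical analyses is a crossover model in which each patient has a treated and an untreated phase, and the shift cancels from the phase-averaged effect (item 6). This objection stands and limits the point to the comparisons named in items 1 to 5.

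Four further objections stand in part.

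- **Blinding.** Calling the trial simply unblinded would be wrong, since the psychologist is blinded to group. What remains is the patients' and relatives' own answers, effort and withdrawal, which a blinded assessor does not control.
- **BDAE.** It is an examination given by the blinded psychologist, and its repetition and comprehension parts are needed for eligibility. The risk is therefore weaker than for the CAL, and a patient who withdraws early would still have some BDAE scores.
- **Unstated facts.** The article does not say when patients learn their group, how long after allocation the first assessment falls, or who answers the CAL. Unequal loss is possible, not shown, and the offer of therapy to everyone works against it.
- **Size.** It is tempting to express the shift as 13% to 39% of the detectable effect (0.1/0.762 to 0.3/0.762). That rests on a parallel-group inversion of 27 per arm. The design is a crossover and no effect or SD is stated, so the percentage is not established.

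That this is a pilot reported in a condensed article, with its design figure not shown, does not settle the matter. The text itself fixes the order, and Randomization and Primary outcomes agree on it.

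**Conclusion.** The point holds in limited form. The article places the study baseline after allocation in a trial that is open to participants with a blinded assessor. This can bias group 1's pre/post change, the phase-1 therapy-versus-waitlist comparison, and the phase-specific and treatment-by-phase contrasts. It can also make loss before baseline unequal. The risk lies mainly with the CAL.

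It does not bias the phase-averaged treatment effect when data are complete and the scores are the response. With missing assessments that cancellation is no longer assured.

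The size is unknown. The 0.1 to 0.3 SD (change score) and 0.07 to 0.21 SD (adjusted, r = 0.7) for phase 1 are illustrations resting on an assumed shift and correlation, not estimates. The change is worth making because it removes this source of bias at little cost.

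**What to change.** - Complete the baseline CAL and the full BDAE after consent and confirmation of eligibility, but before the web-based system releases the allocation. Make their completion a condition of release.
- Keep word selection and dubbing training after allocation.
- Reconcile Patient population, Randomization, Intervention and Primary outcomes on which BDAE is the study baseline, and on where the baseline session falls for each group.
- If the baseline is in practice already taken before the allocation is known, correct the wording in Primary outcomes to say so.

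The cost is a change in visit order and one check in the randomisation system. No assessment is added and the 27 per arm is unaffected. With the baseline taken before release, the expected allocation-induced shift is zero, and so is the bias from this source.
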